### *Secondary Outcomes*

| Outcome                   | Definition                                       | Measurement                                               | Scoring                                    | Reliability/Validity                                                                                                                                                               |
|---------------------------|--------------------------------------------------|-----------------------------------------------------------|--------------------------------------------|------------------------------------------------------------------------------------------------------------------------------------------------------------------------------------|
| Alcohol-related Knowledge | Understanding of alcohol-related harms and myths | 23 yes/no/don't know items adapted from Eze et al. [31]   | Summed score 0-23; higher = more knowledge | Internal consistency (Cronbach's $\alpha \geq 0.70$ ) and test-retest reliability (ICC $\geq 0.75$ ) will be assessed. Content validity will be established through expert review. |
| Attitude (Direct)         | Overall evaluation of alcohol consumption        | 4 semantic differential items [15,28]                     | Summed score 4-28; higher = more favorable | Cronbach's $\alpha \geq 0.70$ will indicate acceptable internal consistency. ICC $\geq 0.75$ will indicate acceptable test-retest reliability.                                     |
| Attitude (Indirect)       | Belief-based evaluation                          | 12 belief items $\times$ 12 outcome evaluation items [28] | Range: -84 to +84                          | Cronbach's $\alpha \geq 0.70$ will be considered acceptable. Construct validity will be assessed through confirmatory factor analysis.                                             |
| Subjective Norms (Direct) | Perceived social pressure                        | 4 items, 7-point Likert scale [15,28]                     | Summed score 4-28; higher = more approval  | Acceptable reliability will be defined as Cronbach's $\alpha \geq 0.70$ and ICC $\geq 0.75$ .                                                                                      |

| Outcome                                 | Definition                               | Measurement                                        | Scoring                                  | Reliability/Validity                                                                                            |
|-----------------------------------------|------------------------------------------|----------------------------------------------------|------------------------------------------|-----------------------------------------------------------------------------------------------------------------|
| Subjective Norms (Indirect)             | Normative beliefs × motivation to comply | 6 normative belief items × 6 motivation items [28] | Range: -84 to +84                        | Cronbach's $\alpha \geq 0.70$ will indicate acceptable internal consistency.                                    |
| Perceived Behavioral Control (Direct)   | Perceived ability to resist alcohol      | 4 items, 7-point Likert scale [15, 28]             | Summed score 4-28; higher = more control | Cronbach's $\alpha \geq 0.70$ and ICC $\geq 0.75$ will be considered acceptable.                                |
| Perceived Behavioral Control (Indirect) | Control beliefs × perceived power        | 7 control belief items × 7 power items [28]        | Range: -105 to +105                      | Internal consistency will be assessed with Cronbach's $\alpha$ , with $\alpha \geq 0.70$ considered acceptable. |

### Covariates

| Domain         | Variables                                                                                                                                                                                                         |
|----------------|-------------------------------------------------------------------------------------------------------------------------------------------------------------------------------------------------------------------|
| Demographics   | Age (years, categorized as 15-19, 20-24), Sex (male, female), Grade level (9-10 lower secondary, 11-12 upper secondary), Religion (Orthodox, Muslim, Protestant, Other), Ethnicity (Amhara, Oromo, Tigray, Other) |
| Socioeconomic  | Father's education (no formal, primary, secondary, or higher); Mother's education (no formal, primary, secondary, or higher)                                                                                      |
| Family Factors | Family discussion about alcohol (yes/no), parental alcohol use (yes/no)                                                                                                                                           |
| Peer Factors   | Peer alcohol use (yes/no)                                                                                                                                                                                         |

## ***Data Collection Procedures***

### ***Questionnaire Development***

The self-administered questionnaire will be developed through adaptation of standardized TPB questionnaires [28], review of relevant literature [16, 17, 31], incorporation of findings from elicitation study, translation and back-translation (English → Amharic → English), and expert review by public health specialists and language experts.

### ***Pre-testing and Validation***

The questionnaire will be pre-tested with 60 students (30 per school) not included in the main study to assess the following:

- **Internal consistency:** Cronbach's  $\alpha$  will be calculated for each multi-item scale, with  $\alpha \geq 0.70$  considered acceptable
- **Test-retest reliability:** Intra-class correlation coefficients (ICC) will be calculated by administering the questionnaire to the same students two weeks apart, with  $ICC \geq 0.75$  considered acceptable; for the single-item current alcohol use measure, kappa statistic ( $\kappa \geq 0.60$ ) will be used
- **Content validity:** Expert review by public health specialists and language experts will ensure items adequately cover the construct domains
- **Face validity:** Pilot participants will be asked whether items are clear, relevant, and acceptable

### ***Data Collection Schedule***

| Time Point                                | Activity                        | Instruments                                          |
|-------------------------------------------|---------------------------------|------------------------------------------------------|
| Baseline (February 1-7, 2021)             | Self-administered questionnaire | TPB questionnaire, knowledge items, demographic form |
| Intervention (February 8 - March 7, 2021) | 4 weekly sessions               | Session logs, fidelity checklists                    |
| Endline (June 7-15, 2021)                 | Self-administered questionnaire | Same as baseline                                     |

## ***Data Collection Procedures***

### **Baseline Data Collection (Scheduled for February 1-7, 2021):**

- Research assistants will be trained for 2 days on data collection procedures prior to baseline assessment
- Questionnaires will be distributed in classrooms during regular school hours
- Standardized instructions will be read aloud by research assistants to ensure consistency
- Students will complete questionnaires independently, with an expected completion time of 45-60 minutes
- Research assistants will remain in the classroom to answer questions and provide clarification as needed
- Completed questionnaires will be collected immediately to minimize data loss

### **Endline Data Collection (Scheduled for June 7-15, 2021):**

- The same procedures as the baseline will be followed
- Data collection will be conducted three months post-intervention
- The same validated questionnaires will be used to ensure comparability
- Different research assistants will be deployed for endline data collection to maintain blinding and reduce measurement bias

## ***Quality Control Measures***

| Measure               | Description                                             |
|-----------------------|---------------------------------------------------------|
| Standardized training | All data collectors will receive 2-day training         |
| Field manual          | Detailed manual provided to all data collectors         |
| Supervision           | Regular supervision during data collection              |
| Daily checks          | Completed questionnaires checked daily for completeness |
| Immediate feedback    | Corrective action taken when needed                     |
| Double data entry     | Two independent operators to minimize errors            |

## ***Data Management and Statistical Analysis***

### **Data Entry and Management**

| Activity      | Description                                                                                                                                                                                                                                          |
|---------------|------------------------------------------------------------------------------------------------------------------------------------------------------------------------------------------------------------------------------------------------------|
| Data Entry    | Data will be double-entered using EpiData 3.1 software, with range and consistency checks built into entry screens two independent data entry operators; entries will be compared and discrepancies resolved by referring to original questionnaires |
| Data Cleaning | Frequency distributions will be checked for out-of-range values; consistency checks across related variables; missing data patterns will be examined; outliers will be identified and verified                                                       |
| Data Storage  | De-identified data stored on password-protected computers; backup copies will be maintained on secure cloud storage; paper questionnaires will be stored in locked cabinets; access limited to research team members                                 |
| Data Security | Participant identifiers will be removed from the analysis dataset; linking codes will be kept separately from data; secure transfer protocols will be used for data sharing                                                                          |

## ***Statistical Analysis Plan***

### ***Descriptive Analysis***

Descriptive statistics will be computed to summarize the baseline characteristics of study participants:

- **Frequencies and percentages** will be calculated for all categorical variables (e.g., sex, grade level, religion, parental education, family discussion about alcohol, and peer alcohol use).
- **Means and standard deviations** will be computed for continuous variables that are normally distributed (e.g., age, knowledge scores, and TPB construct scores).
- **Medians and interquartile ranges** will be computed for continuous variables that are not normally distributed
- **Tables and figures** will be generated to summarize baseline characteristics and to facilitate comparison between intervention and control groups prior to the intervention

Normality of continuous variables will be assessed using Shapiro-Wilk tests and visual inspection of Q-Q plots prior to selecting appropriate descriptive statistics.

### ***Baseline Comparability:***

| Variable Type                                                                                   | Test                 |
|-------------------------------------------------------------------------------------------------|----------------------|
| Categorical variables                                                                           | Chi-square tests     |
| Continuous variables (normal distribution)                                                      | Independent t-tests  |
| Continuous variables (non-normal distribution)                                                  | Mann-Whitney U tests |
| Variables with $p < 0.05$ will be considered unbalanced and adjusted in multivariable analyses. |                      |
| Within-Group Changes:                                                                    |                      |

| Outcome Type | Test            | Effect Size |
|--------------|-----------------|-------------|
| Continuous   | Paired t-tests  | Cohen's d   |
| Dichotomous  | McNemar's tests | Odds ratios |

### **Between-Group Comparisons:**

| Outcome Type | Test                | Effect Size             |
|--------------|---------------------|-------------------------|
| Continuous   | Independent t-tests | Cohen's d with 95% CI   |
| Dichotomous  | Chi-square tests    | Odds ratios with 95% CI |

**Generalized Estimating Equations (GEE)** will be used to account for clustering at the class level:

| Component             | Specification                                                     |
|-----------------------|-------------------------------------------------------------------|
| Distribution family   | Normal for continuous outcomes; binomial for dichotomous outcomes |
| Link function         | Identity for continuous; logit for dichotomous                    |
| Correlation structure | Exchangeable (assumes equal correlation within clusters)          |

| Component | Specification |
|-----------|---------------|
|-----------|---------------|

|                 |             |
|-----------------|-------------|
| Clustering unit | Class level |
|-----------------|-------------|

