## *Sample Size Determination*

The sample size is calculated using the formula for comparing two proportions in cluster-based studies [24], accounting for the intra-cluster correlation coefficient (ICC). Assuming 80% power, 95% confidence level ( $\alpha = 0.05$ ), baseline prevalence of current alcohol use of 36.8% [9], and expected post-intervention prevalence of 26.8% (representing a 10% absolute reduction), the required sample size was determined. To account for clustering at the class level, an ICC of 0.02 was applied based on similar school-based studies [25], with an average cluster size of 30 students per class, yielding a design effect of 2. After adjusting for a 10% loss to follow-up, the total required sample was 1,496 students (748 per group).

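### The protocol attaches its between-group effect sizes and 95% CIs to t-tests and chi-square tests that ignore class allocation, and does not name the class-level GEE it also plans as primary

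*Protocol*

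**What the plan says.** The Abstract, Study Design and Setting, and Sampling and Allocation Procedure all make the class the unit of allocation. Sample Size Determination allows for this: "an ICC of 0.02 was applied based on similar school-based studies", "with an average cluster size of 30 students per class, yielding a design effect of 2".

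The protocol's Statistical Analysis Plan then describes the comparison between arms in two ways.

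- **Two-sample tests.** The Between-Group Comparisons table gives "Independent t-tests | Cohen's d with 95% CI" for continuous outcomes, and chi-square tests with odds ratios and 95% CIs for dichotomous ones.
- **GEE.** Directly below, generalized estimating equations "will be used to account for clustering at the class level", with family, link, exchangeable correlation and clustering unit specified. Adjusted Variables lists the covariates, including the baseline value of the outcome. Model Fit Assessment adds a sensitivity analysis over correlation structures.

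The Abstract mentions only the GEE and gives it the task of estimating adjusted effects. The GEE table names no effect measure and no confidence interval. No section ranks the two analyses.

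The within-group table under Baseline Comparability plans paired t-tests for continuous outcomes and "McNemar's tests | Odds ratios" for dichotomous ones.

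**The concern.** An independent t-test or a chi-square test takes its standard error from the number of students. When whole classes are allocated and students in a class resemble one another, that standard error is too small, and so are the p-value and the interval. The protocol accepts this when it inflates the sample size, then sets it aside in the table that names its effect sizes and CIs.

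As written, both primary outcomes and all seven secondary outcomes will each have two between-arm results, one of them invalid for this design. Because the Abstract speaks of adjusted effects, the section can be read as using the simple tests for unadjusted results and the GEE for adjusted ones. On that reading, every unadjusted CI and p-value would be wrong. If the two results disagree, the protocol does not say which decides.

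**Working it through.** **Inputs**
- From Sample Size Determination: "Assuming 80% power, 95% confidence level" (two-sided assumed), prevalences 36.8% and 26.8%, ICC 0.02, 30 students per class, stated design effect (DE) 2, loss 10%.
- From Intervention Overview: 25 groups of 30. The same number of control classes is assumed.

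**1. The plan's own sample size**
- n per arm = (1.960 + 0.842)² × [0.368 × 0.632 + 0.268 × 0.732] / 0.10² = 336.5.
- 336.5 × 2 = 673.0, and 673.0 / 0.90 = 747.8, which rounds up to 748 per arm and 1,496 in total. This matches the protocol, so the sample was sized with DE 2.

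**2. Design effect from the stated inputs**
- DE = 1 + (m − 1) × ICC.
- m = 30: 1 + 29 × 0.02 = 1.58, not 2. A DE of 2 would need ICC = 1/29 = 0.034, which is stated nowhere.
- m = 27 (30 less 10% loss): 1 + 26 × 0.02 = 1.52.

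**3. Effect on a test that ignores class**
- Ratio of naive to correct CI width = 1/√DE.
- Actual type I error = 2 × [1 − Φ(1.96/√DE)]. Coverage is 1 minus this.

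| Basis | DE | CI width ratio | CI too narrow by | Type I error | Coverage |
|---|---|---|---|---|---|
| ICC 0.02, 27 analysed | 1.52 | 0.811 | 18.9% | 11.2% | 88.8% |
| ICC 0.02, 30 per class | 1.58 | 0.796 | 20.4% | 11.9% | 88.1% |
| DE as stated | 2 | 0.707 | 29.3% | 16.6% | 83.4% |

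**4. Check by simulation**
- Independent t-test, 25 against 25 classes of 30, no true effect, 20,000 runs: 12.1% rejections at ICC 0.02 and 16.3% at ICC 0.034.
- 25 classes of 27 per arm, ICC 0.02, 4,000 runs: 11% for the naive test and about 5% for a class-level GEE.

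**5. Is the naive interval always narrower than the planned GEE interval?**
The GEE adjusts for the baseline value and the t-test does not. For a continuous outcome with pre-post correlation r, the ratio of GEE to naive standard error is roughly √[DE × (1 − r²)]. The documents do not give r, so a range is shown at DE 1.52.

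| r | 0 | 0.3 | 0.5 | 0.6 | 0.7 |
|---|---|---|---|---|---|
| Formula | 1.23 | 1.18 | 1.07 | 0.99 | 0.88 |
| Simulated | 1.21 | 1.16 | 1.06 | 0.97 | 0.87 |

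The ratio falls below 1 once r is about 0.6.

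**The case against.** The strongest reply is that a valid analysis is already planned. The GEE is specified in some detail, the Abstract mentions no other method, and the natural order of the section is a crude comparison followed by an adjusted one. That stands, and it limits the point: the trial does not lack a cluster-aware analysis. It does not remove the point. The protocol attaches its named effect sizes and CIs to the simple tests and nowhere calls them crude. A separate statistical analysis plan might add a ranking, but the fault lies in what the protocol's own analysis section states.

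Four stronger readings are tempting, and the documents do not support them.

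- *The trial's conclusions carry a false-positive rate of 12-17%.* The inflation affects only conclusions drawn from the t-test and chi-square results, not from the GEE.
- *The upper figures, 16.6% and 29%, are a plausible level of clustering.* They rest on a DE of 2 that the stated ICC and class size do not produce.
- *The unclustered result will always look more favourable.* With baseline adjustment the GEE may be the more precise of the two (step 5). The naive interval is invalid either way.
- *The within-arm tests are offered as tests of the intervention.* The protocol calls them within-group changes and makes no such claim.

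**Conclusion.** The point holds for the t-test and chi-square results. Their between-group CIs and p-values are wrong for a design that allocates classes, and the protocol leaves them free to carry the conclusion. With 27-30 students analysed per class and ICC 0.02, the type I error is about 11-12% instead of 5%, and CIs are about 19-20% too narrow. The larger figures apply only if the stated DE of 2 is taken at face value.

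This rests on three assumptions:
- The planning ICC applies. It is given for sizing on current alcohol use, and no ICC is stated for intention or the other scores.
- Class sizes are roughly equal.
- Stratifying allocation by grade within school does not remove much of the between-class variation. It may remove some, which would lower the figures.

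**What to change.** - Name the class-level GEE as the primary analysis of both primary outcomes.
- Take all between-group estimates, 95% CIs and p-values from it: a mean or standardised difference for scores, an odds ratio for current alcohol use.
- Remove the t-test and chi-square rows as inference, or label them crude and descriptive, without p-values or CIs.
- State that within-arm paired t and McNemar results are not evidence of an intervention effect, since change within one arm mixes that effect with time and retest effects.

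The cost is wording only, because the GEE is already specified. Unadjusted CIs widen, by a factor of about √1.52 = 1.23 to √1.58 = 1.26 at ICC 0.02. Baseline-adjusted GEE CIs may be wider or narrower than the naive ones, depending on the pre-post correlation.

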**Adjusted Variables:**

- Baseline value of outcome variable
- Father's education
- Mother's education
- Family discussion about alcohol
- Baseline alcohol use status

**Model Fit Assessment:**

- Quasi-likelihood under Independence Model Criterion (QIC) for model comparison
- Examination of residuals
- Sensitivity analysis using different correlation structures

**Software**

|                      |                 |
|----------------------|-----------------|
| Purpose              | Software        |
| Data entry           | EpiData 3.1     |
| Statistical analysis | SPSS version 25 |

***Handling of Missing Data***

**Missing Data Assessment:**

- The proportion of missing data will be calculated for each variable

**Handling Strategy:**

- **Complete-case analysis** will be conducted for the primary analysis, as the anticipated proportion of missing data is low (< 2%).
- **Multiple imputation** using chained equations will be performed if missing data exceed 5% to reduce potential bias and preserve statistical power

